### Participants

A total of 166 participants with a diagnosis of DM will be recruited into the RCT. Inclusion criteria are: (1) have a DM diagnosis, confirmed by medical records; (2) be aged 18 years or above; and (3) be able to converse in English without an interpreter. Exclusion criteria are: (1) presence of developmental disability or amnestic syndrome impairing their ability to learn from the intervention; and (2) comorbid serious acute medical illness defined by the treating physician. As the OHP adopts a holistic approach to managing chronic disease, patients may enter the program at any stage along the continuum of care. De-identified records will be collected on how many people with diabetes were approached or self-referred to the study including reasons for decline, to assess for potential selection bias.

Power was calculated to detect a medium effect size of d = 0.50. This was chosen as a clinically meaningful effect size that may be compared with previous RCT research in the area of chronic disease management programs [28]. The calculations assumed two primary outcomes (health-related quality of life and General Self-efficacy Scale (GSE) scores), four assessment points (baseline, 3-month, 6-month, and 12-month follow-ups), a study-wide type I error rate (α) of .05, and hence a type II error rate (β) of 0.20 (power of 0.80), a correlation of post-treatment scores with baseline measurements (ρ) of 0.81, and a two-tailed statistical test [29]. To detect the effect size of d = 0.50, 66 participants in each of the control and intervention groups will be required. Allowing for up to 20 % attrition, a total of 166 participants, or 83 in each group will be recruited.

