### Statistical analyses

Intention-to-treat analyses will be employed to prevent overestimation of efficacy. Categorical variables will be analysed using chi-squared tests (or Fisher’s exact test for small samples). A mixed-effects model, repeated measures (MMRM) approach will be used to examine the longitudinal profile of all continuous variables at 3, 6 and 12 months post-baseline. For all MMRM analyses, baseline scores will be used as covariates and the models will include prespecified fixed effects of treatment, clinician, and time, and treatment-by-time and treatment-by-clinician interactions.

Secondary analyses using analysis of covariance will be conducted to compare change scores during treatment and follow-up phases for all primary, secondary, and process outcomes using the fixed, continuous covariate of baseline score and time from diagnosis as well as the categorical fixed effects of treatment group, clinician, and treatment-by-clinician interactions. Sub-analyses will be conducted on participants with T1 and T2DM as these have different disease processes and aetiologies.

Although the attrition rate is not expected to vary by treatment condition, we will attempt to identify key predictors of attrition status (i.e. demographic and baseline clinical characteristics) and test for differences between conditions. Assuming the data are missing at random, several procedures offer effective approaches that may attenuate attrition. Maximum likelihood models (i.e. MMRM), with time as a random variable, allow the use of all available data from all assessments, reducing bias and increasing power [46]. In addition, multiple imputation procedures that utilise the expectation-maximization (EM) algorithm with bootstrap estimates of standard errors will be used to address attrition. The application of these procedures can provide unbiased estimates, even in the face of substantial missing data [47].

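### The MMRM lets the treatment effect, but not the baseline slope, vary by visit; a baseline-by-time term would protect the 12-month estimate at almost no cost

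*Protocol article*

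**What the plan says.** The Statistical analyses section applies an MMRM to "the longitudinal profile of all continuous variables at 3, 6 and 12 months post-baseline". It says: "For all MMRM analyses, baseline scores will be used as covariates". It then gives the models "prespecified fixed effects of treatment, clinician, and time, and treatment-by-time and treatment-by-clinician interactions". Two interactions are named; baseline-by-time is not one of them.

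The same section assumes data missing at random, expects similar attrition rates in the two arms, and plans to look for baseline predictors of attrition and for differences between arms. It adds multiple imputation, and says of its likelihood and imputation procedures that they "can provide unbiased estimates, even in the face of substantial missing data".

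The Participants section gives one correlation between baseline and post-treatment scores, 0.81, and does not say whether it holds at every visit.

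**The concern.** A main effect of baseline without a baseline-by-time term forces one slope on all three visits. Should the association with baseline weaken over follow-up, a common slope driven by the earlier visits over-adjusts at month 12. Likelihood estimation under missing at random relies on a correct mean model, so an incorrect slope can matter once participants are lost.

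Month 12 is the last assessment. It shows whether the effect of an 8-week programme with one booster lasts, and cumulative drop-out is greatest there. The model applies to every continuous outcome, so a constant slope is being assumed for all of those scales.

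**Working it through.** **1. The plan's own figure.** Inputs from Participants: "Power was calculated to detect a medium effect size of d = 0.50", "a study-wide type I error rate (α) of .05", two-sided, power 0.80, ρ = 0.81, four assessments; "The calculations assumed two primary outcomes". The article gives no formula. One route that reproduces its figure splits alpha over two outcomes (0.025 each):

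- 2(z₀.₉₈₇₅ + z₀.₈₀)²/d² = 2(2.241 + 0.842)²/0.25 ≈ 76.04 per arm.
- Repeated-measures factor (1 + 3 × 0.81)/4 = 0.8575, and 76.04 × 0.8575 = 65.2, so 66 per arm.
- 66/0.80 = 82.5, so 83 per arm and 166 in total.

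Baseline-by-time does not enter this calculation, so the sample size stands.

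**2. Mechanism.** Let b₁₂ be the true baseline slope at month 12, b_c the fitted common slope, and Δx the difference between arms in mean baseline. With complete data, and leaving clinician terms aside, the common-slope estimate at month 12 is the difference in month-12 means minus b_c·Δx. Its error from a wrong slope is therefore (b₁₂ − b_c)·Δx. Randomisation makes Δx zero on average, so a wrong slope alone adds variance but no bias. Bias also needs drop-out that shifts baseline differently in the two arms. With drop-out, the earlier visits of those who leave also contribute, so the size has to be simulated.

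**3. Simulation.** From the protocol: 83 per arm, true effect 0.50 SD, about 20% drop-out. Assumed: monotone drop-out, the pattern of baseline correlations, correlation 0.81 between post-baseline visits, unstructured covariance, no clinician terms, outcome SD of 1 (so slope equals correlation). There were 4000 runs per row. *One arm* means that drop-out depends on baseline in one arm only; *opposite* means that it does so in opposite directions in the two arms. Each cell gives common slope / visit-specific slope, for the 12-month effect.

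| Baseline correlation at 3/6/12 months | Drop-out | Bias (SD) | Mean SE | 95% CI coverage |
|---|---|---|---|---|
| 0.81/0.81/0.81 | none | −0.0016 / −0.0015 | 0.0908 / 0.0910 | 0.9473 / 0.9477 |
| 0.81/0.81/0.81 | opposite | −0.0016 / −0.0019 | 0.1011 / 0.1025 | 0.9493 / 0.9507 |
| 0.81/0.75/0.68 | none | −0.0033 / −0.0027 | 0.1149 / 0.1140 | 0.9517 / 0.9540 |
| 0.81/0.75/0.68 | one arm | −0.0196 / 0.0011 | 0.1250 / 0.1243 | 0.9423 / 0.9433 |
| 0.81/0.75/0.68 | opposite | −0.0397 / 0.0004 | 0.1254 / 0.1257 | 0.9330 / 0.9430 |
| 0.81/0.70/0.55 | none | 0.0013 / 0.0013 | 0.1371 / 0.1300 | 0.9453 / 0.9463 |
| 0.81/0.70/0.55 | one arm | −0.0471 / −0.0028 | 0.1463 / 0.1395 | 0.9305 / 0.9453 |
| 0.81/0.70/0.55 | opposite | −0.0919 / −0.0028 | 0.1463 / 0.1409 | 0.9028 / 0.9457 |

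The Monte Carlo error of each bias is the SD of the estimates over √4000, about 0.001 to 0.002.

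Hand check of the visit-specific SE with no drop-out, √(2(1 − ρ₁₂²)/83): 0.091 for 0.81, 0.114 for 0.68 and 0.130 for 0.55, as in the table.

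**4. Reading the table.**

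- SE loss with no drop-out: 0.1149/0.1140 = 1.008 and 0.1371/0.1300 = 1.055, so about 1% to 5%.
- Bias relative to d: 0.0196/0.50 = 4% up to 0.0919/0.50 = 18%.
- Bias relative to its own SE: 0.0196/0.1250 = 0.16 up to 0.0919/0.1463 = 0.63.
- Completely random drop-out, and drop-out depending on baseline equally in both arms (700 runs each), gave bias within simulation error of zero at every correlation pattern.

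**5. A second simulation** took a 12-month correlation of 0.60 or 0.50 and drop-out rates nearly equal by arm (19% to 21% against 19.5%), with low-baseline participants leaving more often in the OHP arm only (log-odds slope 0.6 to 1.0 per SD). Bias was −0.022 to −0.045 SD with a common slope and −0.003 to +0.004 with visit-specific slopes. Under random drop-out the variance ratio was 1.038 to 1.084, or √1.038 = 1.019 to √1.084 = 1.041 in SE.

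**The case against.** The harm rests on two conditions that the article does not establish. The first is a baseline slope that changes between visits. The single correlation of 0.81 is compatible with no change, and a falling correlation need not mean a falling slope, because slope is correlation times the ratio of SDs. The second, needed for bias, is drop-out that depends on baseline differently by arm. The article expects similar attrition rates and will examine predictors of attrition. All of this stands and makes the point conditional. Similar rates do not exclude different dependence on baseline, however: the second simulation kept them nearly equal and still found bias.

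Other parts of the plan may help. The secondary ANCOVA of change scores, if fitted separately by phase, gives each phase its own baseline slope, and multiple imputation may reduce bias. Neither changes the stated main model, and the imputation model is not described.

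It can also be said that a condensed article leaves covariate-by-visit terms to the full plan, and that saying models will include certain effects does not rule out others. That is fair as to severity. But the article calls its effects prespecified and names two interactions, so the model as published has a common slope.

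The simulations assumed an unstructured covariance, which the article does not name. The first left out the clinician terms, and none are reported for the second. The figures therefore show scale and are not predictions.

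A reader might also infer that the MMRM should adjust for time from diagnosis, because the secondary ANCOVA uses "the fixed, continuous covariate of baseline score and time from diagnosis". The article does not support that. A secondary analysis may carry an extra covariate without contradicting the main one. Diagnostic information is to be taken from medical records only where possible (Outcome measurements), so requiring it could remove participants from the main model.

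**Conclusion.** The point holds conditionally and is minor. As written, the MMRM fixes one baseline slope over 3, 6 and 12 months. A changing slope costs about 1% to 5% in the 12-month SE in the scenarios tried without drop-out. A changing slope together with arm-specific dependence of drop-out on baseline biases the 12-month effect by about 0.02 to 0.09 SD, with coverage falling to about 90% at worst. The sign follows the assumed direction of drop-out. The slope patterns and drop-out models are assumptions.

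A reader might conclude that the 12-month effect will be biased, or that the article's statement on unbiased estimation is wrong. The documents support neither: a common slope alone gave no bias, and that statement says what the procedures can achieve without guaranteeing it for one model.

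The case for change is that the trade is one-sided. The extra term removed the bias wherever it arose. With a constant slope it left the SE essentially unchanged without drop-out (0.0910 against 0.0908) and raised it by about 1% under opposite-direction drop-out (0.1025 against 0.1011).

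**What to change.** Add a baseline-by-time interaction, with time as a categorical visit, to the listed fixed effects of every MMRM, so that each visit has its own baseline slope. With three post-baseline visits this uses two extra degrees of freedom. It takes one line of text and needs no new data and no change to the sample size. Leave time from diagnosis in the secondary ANCOVA only.

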A Cochrane review of psychological and pharmacological interventions for depression in DM (eight RCTs; n = 1122) found a moderate and clinically significant effect on depression [6]. Also noted was sparse and inconclusive evidence in relation to the influence of psychological intervention on blood glucose levels, largely due to substantial risk of bias and heterogeneity of populations and interventions [6]. Similar findings regarding CBT and glycaemic control in DM were also reported in another systematic review and meta-analysis (eight studies; n = 1547), which revealed a non-significant trend towards improved blood sugar levels (BSLs) [19].

Recent evidence has established that effective disease management of DM requires strengthening of psychosocial skills, ideally within a collaborative therapy framework integrated with usual medical care [4, 5, 16]. A number of challenges have also been noted including: cost-effectiveness, participation and attrition rates, and delivery that complements and coexists with usual DM health care [6, 17, 18]. As DM has reached epidemic proportions [1]; new and innovative ways of managing it are essential. The MINDS Optimal Health Program (MINDS OHP) adopts a collaborative therapy approach that offers structured yet individualised multidisciplinary support and education to enhance self-efficacy and the psychosocial wellbeing of people with type 1 and type 2 DM. The program recognises that though there are shared psychosocial impacts, type 1 and type 2 diabetes have separate aetiologies and disease processes which will be taken into account in delivering and evaluating the MINDS OHP.

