### Setting

The study will be conducted at St Vincent’s Hospital, a large metropolitan teaching hospital in Melbourne, Australia. As of March 2015 the endocrinology and diabetes unit had over 1000 people with diabetes enrolled in their patient database: 370 people with type I DM and 1313 with type 2 DM. The necessary volume of clinical cases and expertise required for this study is well established in this unit. As a focus of the OHP is care co-ordination, the program has been integrated into existing services through transparent, planned and close collaboration with the diabetes unit, i.e. diabetes educators, endocrinologists, social workers, and dieticians.

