#### Randomisation and blinding

Using a computer-generated block randomisation sequence created by a person not directly involved in the study, participants will be allocated to treatment or control group. The allocation sequence will be generated using random numbers. Participants will be randomised progressively as they consent. Due to the nature and length of the intervention, it is not possible to mask either participant or investigator to the treatment allocation.

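### Sub-analyses by diabetes type are planned, but neither diabetes type nor a treatment-by-type term is among the listed model terms, so no stated model tests whether the effect differs by type

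*Protocol article*

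**What the plan says.** All places are in the protocol article.

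- Statistical analyses, on type: "Sub-analyses will be conducted on participants with T1 and T2DM as these have different disease processes and aetiologies". No method for these sub-analyses is given.
- Statistical analyses, mixed model for repeated measures: baseline score as covariate, plus "prespecified fixed effects of treatment, clinician, and time, and treatment-by-time and treatment-by-clinician interactions".
- Statistical analyses, analysis of covariance: baseline score and time from diagnosis as continuous covariates, plus "categorical fixed effects of treatment group, clinician, and treatment-by-clinician interactions".
- Diabetes psychosocial interventions: "type 1 and type 2 diabetes have separate aetiologies and disease processes which will be taken into account in delivering and evaluating the MINDS OHP".
- Participants: "Power was calculated to detect a medium effect size of d = 0.50". This concerns the whole trial; no figure is given for either type.
- Setting: the clinic database held "370 people with type I DM and 1313 with type 2 DM".
- Randomisation and blinding: "Using a computer-generated block randomisation sequence created by a person not directly involved in the study". Stratification by type is not mentioned.

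**The concern.** The plan names its covariates and interactions one by one. Diabetes type is in neither list, although the plan singles it out as a reason for sub-analysis and says it will be taken into account in the evaluation. The most natural reading of the sub-analysis sentence is that the models are run within each type. That gives an effect estimate per type, but it does not by itself test whether the two effects differ.

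The risk lies in how the two results are then read. The types are likely to differ in number, so their tests would differ in power. A reader who sees significance in one type and not in the other may conclude that the program works in only one of them. With the same true effect in both types, that pattern can be common. The Discussion foresees moving the program into a hospital referral pathway if findings are positive, so a false contrast between types could affect who is referred.

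A smaller point is that type is a baseline characteristic and is not adjusted for in the main model, so a chance imbalance between arms would go uncorrected.

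**Working it through.** **Step 1. Reproduce the planned sample size.** Inputs from Participants: d = 0.50, study-wide alpha 0.05, power 0.80, correlation 0.81, four assessments, two-tailed; "The calculations assumed two primary outcomes". The formula is not stated. Splitting alpha over two outcomes (0.025 each) and averaging four equally correlated measurements is my inference, made because it returns the stated number:

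- n per arm = 2 × ((2.241 + 0.842)/0.50)² = 76.04 before the repeated-measures factor
- factor = (1 + 3 × 0.81)/4 = 0.8575
- 76.04 × 0.8575 = 65.2, so 66 per arm, as stated
- 66/0.80 = 82.5, so 83 per arm and 166 in total, as stated

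Below, 0.8575 is the design variance. The alternative is the covariance-adjusted variance at one visit, 1 − 0.81² = 0.3439. That factor does not return 66 (it gives 22 at alpha 0.05 and 27 at 0.025), but it may be closer to what the baseline-adjusted models achieve.

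**Step 2. Subgroup sizes.** Clinic mix from Setting: 370/(370 + 1313) = 370/1683 = 22% type 1. Applying it to the trial is an assumption. Because community recruitment may change the mix, I range the share from 22% to 50%. At 22%, 66 evaluable per arm gives 66 × 0.22 = 14.5 with type 1 and 51.5 with type 2.

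**Step 3. Power within each type, same true d = 0.50.** With variance factor f, SE = √(2f/n) and power ≈ Φ(d/SE − z). At 22% type 1, design variance, alpha 0.025:

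- Type 1: SE = √(2 × 0.8575/14.52) = 0.344; 0.50/0.344 = 1.455; power 0.216
- Type 2: SE = √(2 × 0.8575/51.48) = 0.183; 0.50/0.183 = 2.739; power 0.691

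**Step 4. Chance that exactly one type is significant.** p₁(1 − p₂) + p₂(1 − p₁) = 0.216 × 0.309 + 0.691 × 0.784 = 0.067 + 0.542 = 0.61. Most of this (0.54) is type 2 significant and type 1 not.

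| Type 1 share | Design variance, alpha 0.025 | Design variance, alpha 0.05 | Covariance-adjusted, alpha 0.05 |
|---|---|---|---|
| 22% | 61% | 61% | 37% |
| 30% | 56% | 55% | 24% |
| 40% | 51% | 50% | 15% |
| 50% | 50% | 48% | 12% |

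Using the t distribution instead of the normal raises the 37% to 40%. At true d = 0.25 the ranges are 22–23%, 31–33% and 48–55% for the three columns. With no effect in either type the chance is 2 × 0.025 × 0.975 = 4.9% or 2 × 0.05 × 0.95 = 9.5%.

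**Step 5. What the interaction test could detect.** SE of the difference = √(SE₁² + SE₂²). At 22%, design variance: √(0.344² + 0.183²) = 0.389. Power for a 0.5 SD difference between types at alpha 0.025 is Φ(0.50/0.389 − 2.241) = 0.17.

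| Variance, alpha | Power for a 0.5 SD difference (22% to 50% type 1) | Difference detectable with 80% power |
|---|---|---|
| Design, 0.025 | 17% to 25% | 1.20 to 0.99 SD |
| Design, 0.05 | 25% to 34% | 1.09 to 0.90 SD |
| Covariance-adjusted, 0.05 | 53% to 69% | 0.69 to 0.57 SD |

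**Step 6. Chance imbalance in type.** If randomisation is not stratified by type, the SD of the between-arm difference in type 1 share at 22% is √(0.22 × 0.78 × 2/83) = 0.064. A difference above 10 points is 0.10/0.064 = 1.56 SDs, with probability about 12%.

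**The case against.** The strongest reply is that much of this rests on one sentence in a condensed article. Several stronger readings are tempting, and the documents do not support them.

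- **A reader might infer that the plan chose separate analyses in place of an interaction test.** It does not say so. The subgroup method is unstated, and a full protocol or analysis plan that is not shown may contain the test. What stands is narrower: the term lists that are given omit type.
- **A reader might infer that the sub-analyses cannot show a differing effect.** That is too strong. Two independent estimates with standard errors can be contrasted, which is in effect the interaction test. The error would lie in comparing significance verdicts, and the article does not propose that.
- **A reader might infer that a spurious difference is the usual outcome.** The chance depends on the true effect, the variance and the type 1 share. It is 5–10% with no effect and as low as 12% at d = 0.50 under the smaller variance.
- **A reader might infer a hypothesis that the types respond differently.** The stated reason is different disease processes and causes. No listed objective compares types, and estimating the effect within each is a legitimate descriptive aim.
- **A reader might infer that omitting type biases the main comparison.** Randomisation protects it, chance imbalance is reflected in the standard error, and the baseline score is already a covariate and may absorb much of any difference in level between types. Adding type is a gain in precision and protection against imbalance, not the correction of a bias. The article may also simply not mention stratification.

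The interaction test is itself weak here. That limits what the remedy can deliver, but it also means that comparing within-type verdicts is no better a substitute.

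**Conclusion.** The point holds in a limited form. The listed models contain neither type nor treatment-by-type, so no stated model tests whether the effect differs between type 1 and type 2 diabetes. The figures in steps 4 and 5 show why this should be settled before results are read: with one common effect of the planned size, split verdicts between types could be about as likely as not under the design variance. They are conditional on an identical effect in both types, 66 evaluable per arm, a type 1 share of 22–50%, an inferred split of alpha and correlation structure, and a reader who compares significance. None of this invalidates the primary comparison. It is a modest improvement to the stated analysis.

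**What to change.** Three changes to the Statistical analyses section:

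1. Add diabetes type as a fixed covariate in the primary mixed model. It is a baseline variable that should be obtainable from the diagnosis, which the inclusion criteria require to be confirmed by medical records.
2. Obtain type-specific treatment estimates with confidence intervals from one full-sample model with treatment-by-type and treatment-by-type-by-time terms.
3. State that the interaction estimate and its interval are the only basis for any claim that the effect differs by type, and that this analysis is exploratory.

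The cost is wording and a few model terms; no added visit or participant is needed. Since medical records are reviewed for diagnostic information only where possible, recording type at enrolment should be confirmed. The downside to state openly is the low power shown in step 5: a non-significant interaction must not be read as evidence that the effect is the same in both types.
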